### Data procurement

Demographic findings, comorbidities, and functional capacity will be prospectively collected before surgery. Electrocardiography, chest X-ray, and laboratory results, including troponin I or T and NT-proBNP levels, will be gathered preoperatively within 90 days before surgery and postoperatively within 3 days after surgery. The samples will be analyzed in the respective institutions. Information on surgery, such as operation time, amount of blood loss and blood transfusion, and anesthetic method, will be collected from operation records after surgery. All data will be anonymized and collected on structured case reporting forms (Additional file 2) and recorded in the iCReaT system provided by the Korea Disease Control and Prevention Agency.

To evaluate the discriminatory predictive power of preoperative echocardiography in the prediction of postoperative CVE compared with clinical risk factors, we will obtain traditional risk indices including Revised Cardiac Risk Index (RCRI) [11], Myocardial Infarction and Cardiac Arrest (MICA) score [10], and American College of Surgeons National Surgical Quality Improvement Program (ACS NSQIP) surgical risk calculator [23].

### Echocardiography

Transthoracic echocardiographic images and measurements will be obtained at individual hospitals according to guidelines from the American Society of Echocardiography [24]. Left ventricular dimensions are measured in the parasternal long-axis window. LV volumes and ejection fraction are estimated by modified Simpson’s method, and left atrial volume index is measured by the biplane area-length method and adjusted to body surface area. The presence of RWMA is evaluated based on the 17-segment model of the American Heart Association [25]. Indices of diastolic function will be obtained including the peak early diastolic trans-mitral flow velocity (E), the peak late diastolic trans-mitral flow velocity (A), E/A ratio, deceleration time, the early diastolic mitral annular velocity from the septal annulus (e′), E/e′ ratio, maximal velocity of tricuspid regurgitation, and size of inferior vena cava. To detect significant valvular heart disease, conventional or color Doppler interrogation to four cardiac valves will be performed. To measure LV global longitudinal strain, apical 4-, 2-, and 3-chamber images are acquired following the Digital Imaging and Communications in Medicine format and will be analyzed in the core laboratory by a specialist. All echocardiographic parameters obtained will be used in the post hoc analysis for the discovery of the potential predictor of postoperative CVE.

### Statistical analysis

#### RCT for intermediate-risk group

For continuous variables, data will be presented as means with standard deviation or medians with the interquartile range as appropriate. Categorical variables will be reported as the frequencies with percentiles. The baseline characteristics will be compared using the absolute standardized difference between the two groups. The variables will be perceived as imbalanced when an absolute standardized difference > 0.10. Univariable and multivariable logistic regression analysis will be used to identify significant independent variables associated with the development of endpoints. The effect of covariates on the outcome will be presented as odds ratio and 95% confidence intervals.

#### Prospective cohort study for the high-risk group

Baseline characteristics and the endpoints will be analyzed using the same analysis as RCT with correction for confounding variables. Because of the risk of selection bias, the primary endpoint will be analyzed additionally using propensity score matching as a sensitivity analysis.

All endpoints will be analyzed in the full analysis set and tested supplementally in the per-protocol set. The outcomes will be analyzed according to the assigned group, regardless of performing echocardiography or not, for the full analysis set (intention-to-treat analysis). For per-protocol analyses, subjects without endpoints or who violate the study protocol, such as inability to interpret echocardiography due to poor echo window, will be excluded. All individual components composing primary and secondary endpoints occurring within 30 days after index surgery are documented with the date of occurrence. Additional analysis of each individual component will be performed separately using logistic regression. Sensitivity analysis using the Fine-Gray model for the competing risk will be assessed for the competing risk of all-cause death [26].

Statistical analysis will be conducted using SAS (version 9.4, SAS Institute Inc., Cary, NC, USA). Findings with two-sided *p*-values less than 5% will be considered significant. All statistical analyses will be performed by the Biostatistics Collaboration Unit of Yonsei University College of Medicine.

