### Randomization and stratification

Informed consent was achieved before screening and enrollment for all participants. Patients in the intermediate-risk group will be randomized to receive echocardiography or not, according to block randomization. An independent organization will generate a random table and assign randomization codes to the subjects using an interactive web response system of the Internet-based Clinical Research and Trial management system (iCReaT, version 2.0). The randomization will be performed on an institutional basis to prevent bias.

Patients in the high-risk group will be enrolled consecutively in the prospective cohort study irrespective of the implementation of preoperative echocardiography or not. The use of TTE is at the discretion of attending physicians. To reduce the risk of selection bias according to age, we will stratify the subjects according to the age of 65 years (Fig. 2).

For both studies, usual postoperative care including drug prescriptions or laboratory examinations can be performed as circumstances demand. Trial discontinuation or modifying allocated intervention can be permitted in case of the participants’ request or the medical need for echocardiography before surgery.

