### Sample size calculation

The European Society of Cardiology guidelines indicate that the risk of MI and cardiac death within 30 days after surgery for the intermediate- and high-risk surgery cohorts are 1–5% and >5%, respectively [8]. As we defined the outcomes and the risk groups differently than in previous studies, we hypothesize that the incidence of the primary endpoint without preoperative echocardiography would be 4% in the intermediate-risk group. In the high-risk group, the risk of the primary endpoint was estimated to be 7% in patients under the age of 65 years old and 10% in patients older than 65 years old. The risk of the primary endpoint is assumed to be decreased by 50% in the preoperative echocardiography group. We calculated the requisite number of participants to reach a power of 80%, type I error of 5%, and a loss to follow-up of 2%. A total of 2,330 patients in the intermediate-risk group will be enrolled in the RCT (Fig. 1). For the prospective cohort study, 1,298 participants receiving preoperative TTE and 886 participants not receiving TTE are needed in each group stratified by age of 65 years (Fig. 2).

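### The high-risk cohort has no assigned groups for its intention-to-treat rule, and its 1,298/886 sample size and 80% power are 1:1 age-stratum figures labelled as TTE and no-TTE counts

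*Protocol article*

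**What the plan says.** The protocol article runs two studies: an RCT in the intermediate-risk group and a prospective cohort in the high-risk group.

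- *Randomization and stratification*: cohort patients are enrolled consecutively whether or not they have echocardiography. "The use of TTE is at the discretion of attending physicians". Stratification at age 65 is the step named there against selection bias by age.
- *Sample size calculation*: the cohort's primary-endpoint risk is put at "7% in patients under the age of 65 years old and 10% in patients older than 65 years old", and "The risk of the primary endpoint is assumed to be decreased by 50% in the preoperative echocardiography group". The design targets are "a power of 80%, type I error of 5%, and a loss to follow-up of 2" per cent. The result is given as "1,298 participants receiving preoperative TTE and 886 participants not receiving TTE are needed in each group stratified by age of 65 years". The Abstract gives the cohort total as 2184.
- *Statistical analysis, Prospective cohort study for the high-risk group*: endpoints are to be analysed as in the RCT, with correction for confounders, and propensity score matching is a sensitivity analysis of the primary endpoint. The next paragraph covers all endpoints and sets the analysis set: "The outcomes will be analyzed according to the assigned group, regardless of performing echocardiography or not, for the full analysis set (intention-to-treat analysis"). The same section sets the test level: "Findings with two-sided *p*-values less than 5% will be considered significant".

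**The concern.** The intention-to-treat sentence needs an assigned group and tells the analyst to ignore whether echocardiography was done. In the cohort nothing is assigned, and whether echocardiography was done is the only exposure there is. Taken as written, the rule leaves the cohort without comparison groups. The planned confounder correction and propensity matching do not fill the gap, because both need a defined exposure.

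The sample-size sentence raises a second problem. It presents 1,298 and 886 as TTE and no-TTE counts within an age stratification, but they do not behave like such counts. If they are really age-stratum totals for balanced comparisons, the 80% power depends on an equal TTE split that consecutive enrolment and discretionary TTE do not secure. A reader of the article could not see that condition.

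**Working it through.** **Inputs.** From *Sample size calculation*: risk without TTE of 7% (younger) and 10% (older), a 50% relative reduction (to 3.5% and 5%), 80% power, 5% type I error, 2% loss. Two-sided testing is from *Statistical analysis*. Allocation within the cohort is not stated.

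**Step 1: reproduce the stated size.** Two proportions, 1:1, pooled variance under the null, no continuity correction:

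n per arm = [1.960·√(2p̄(1−p̄)) + 0.8416·√(p₀(1−p₀)+p₁(1−p₁))]² / (p₀−p₁)², then divided by 0.98.

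- Younger stratum, p̄ = 0.0525: (0.6182 + 0.2646)² / 0.035² = 636.3. Then 636.3/0.98 = 649.2, and doubled 1,298.5. Stated: 1,298.
- Older stratum, p̄ = 0.075: (0.7301 + 0.3121)² / 0.05² = 434.4. Then 434.4/0.98 = 443.3, and doubled 886.6. Stated: 886.
- Check on the RCT, 4% v 2%: 1,140.8, rounded up to 1,141 per arm; 1,141/0.98 rounded up is 1,165; doubled 2,330. Stated: 2,330.

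Rounding up at each step gives 1,300 and 888 for the cohort, within 2 patients of the stated figures. Continuity-corrected (1,416 and 968) and one-sided (1,026 and 700) versions do not fit.

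**Step 2: test the labels.**

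- If each age stratum needed 1,298 with TTE and 886 without, the total would be 2 × (1,298 + 886) = 4,368, against the stated 2,184. Power would be 95% and 99%, not 80%.
- If 1,298 v 886 were one comparison at that ratio, 80% power would need 767 + 523 patients at a 7% risk or 524 + 357 at 10%, before loss. Neither fits.
- As two age-stratum totals, 1,298 + 886 = 2,184, which matches the Abstract, and both numbers follow from the inputs.

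**Step 3: power when the split is not controlled.** Hold each stratum at its stated size with 2% loss, so N = 1,298 × 0.98 = 1,272 and 886 × 0.98 = 868. Let f be the TTE share, an assumption because the documents give none. With p̄ = f·p₁ + (1−f)·p₀:

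Power = Φ{[(p₀−p₁) − 1.960·√(p̄(1−p̄)(1/(Nf)+1/(N(1−f))))] / √(p₀(1−p₀)/(N(1−f)) + p₁(1−p₁)/(Nf))}

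Example, younger stratum, f = 0.8: 1,018 with TTE and 254 without, p̄ = 0.042. The null standard error is 0.01406 and the alternative 0.01700. (0.035 − 1.960 × 0.01406)/0.01700 = 0.438, so power is 67%.

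The pooled column uses 2,184 × 0.98 patients and a mixed control risk of (1,298 × 7% + 886 × 10%)/2,184 = 8.2%. It assumes the strata fill as planned and have the same TTE share.

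| TTE share | Younger | Older | Pooled, unadjusted |
|---|---|---|---|
| 20% | 55% | 55% | 87% |
| 30% | 70% | 70% | 95% |
| 40% | 77% | 77% | 97% |
| 50% | 80% | 80% | 98% |
| 60% | 79% | 79% | 97% |
| 70% | 76% | 76% | 95% |
| 80% | 67% | 67% | 90% |
| 90% | 50% | 49% | 73% |

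**Step 4: adjustment.** The size has no term for confounder adjustment, which belongs to the main cohort analysis. If covariates explain a fraction R² of TTE use (also an assumption), the effective size is about N(1−R²). At a 50:50 split, per-stratum power is then 76%, 71% and 65% for R² of 0.1, 0.2 and 0.3.

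**The case against.** The best defence is that the paragraph holding the intention-to-treat sentence looks like common text for both studies. The RCT subsection names no analysis set, and this paragraph goes on to cover all endpoints, software and significance level. On that view the sentence describes the RCT and has only been misplaced. That is probably the intent, but the sentence stands under the cohort heading with no limit to the RCT, and the cohort's own groups are defined nowhere else in the analysis text. The point stands, though the cure is small.

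The 1:1 reading is a reconstruction, and Fig. 2, to which the sample-size text refers, is not shown. The match on both numbers and on the total is close enough to rely on, but the relabelling should be checked against that figure.

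Three stronger readings are tempting, and the documents do not support them:

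- A reader might infer that the cohort is analysed as though TTE had been allocated, with confounding ignored. It is not: confounder correction and propensity matching are both planned.
- A reader might infer that the 80% power is simply false. It is conditional. The TTE share is unknown, per-stratum power stays at 77–80% for shares of 40–60%, and a pooled unadjusted test keeps at least 87% for shares of 20–80%.
- A reader might infer an inflated false-positive rate from two age-stratum tests, or a fixed loss of patients from 1:1 matching. No passage says that each stratum is tested separately for success, and none gives a matching ratio.

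**Conclusion.** Wrong as written, on three linked points.

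1. The assigned-group rule cannot be applied to the cohort, because TTE there is discretionary. This rests on the text alone.
2. The labels on 1,298 and 886 conflict with the stated total (4,368 v 2,184). The numbers are the 1:1 totals of the younger and older strata. This rests on the reproduction above and is subject to Fig. 2.
3. The 80% is a per-stratum figure that holds only near a balanced TTE split and before any loss from adjustment. At an assumed TTE share of 30%, 70%, 80% or 90% it becomes 70%, 76%, 67% or 49–50%. A pooled unadjusted test would exceed 80% over a wide range but falls to 73% at a 90% share. The article does not say which of the two tests the power describes.

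The TTE share and R² are assumptions throughout. What is shown is that the power claim omits its conditions, not that the cohort is underpowered.

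**What to change.** - Limit the intention-to-treat sentence to the RCT.
- Define the cohort groups by whether TTE was actually done between enrolment and surgery, and apply the planned confounder correction and propensity matching to that exposure.
- Relabel 1,298 and 886 as the totals for the younger and older strata, after checking Fig. 2.
- State the TTE split assumed in the calculation, restate the 80% as conditional on it, and say that confounder adjustment lowers it further. A short table by TTE share, as above, would do.
- Say whether the primary cohort test is one pooled test stratified by age or a separate test in each stratum.

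The cost is wording and one table. No extra patients are needed to correct the statement. Keeping 80% in each stratum whatever the uptake would be a different matter: at an 80% TTE share it would take 1,863 and 1,276 patients before any allowance for adjustment. That is a reason to state the claim conditionally, or to rest it on a pooled test.

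### The supplementary per-protocol rule, as worded, keeps only patients with events, and its poor-echo-window example can remove patients only from the TTE group

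*Protocol article*

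**What the plan says.** The rule stands in the protocol article under Statistical analysis, in the subsection on the prospective cohort study for the high-risk group: "subjects without endpoints or who violate the study protocol, such as inability to interpret echocardiography due to poor echo window, will be excluded". The same paragraph gives the set its role: "All endpoints will be analyzed in the full analysis set and tested supplementally in the per-protocol set". The full analysis set follows the assigned group whether or not the echo was done, and the article labels it intention-to-treat. The references to an assigned group and to intention-to-treat indicate that the paragraph also covers the RCT, although it is printed under the cohort heading.

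Two other sentences show how the article uses the word endpoint. The RCT analysis subsection wants to "identify significant independent variables associated with the development of endpoints". The cohort subsection says: "All individual components composing primary and secondary endpoints occurring within 30 days after index surgery are documented with the date of occurrence".

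The groups being compared are set out under Randomization and stratification. For the RCT: "Patients in the intermediate-risk group will be randomized to receive echocardiography or not, according to block randomization". For the cohort: "The use of TTE is at the discretion of attending physicians". The same section allows departures from allocation: "Trial discontinuation or modifying allocated intervention can be permitted in case of the participants’ request or the medical need for echocardiography before surgery".

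**The concern.** In the article an endpoint is something that develops, occurs and has a date. A subject without endpoints is then a patient with no event, and excluding such patients selects the set on the outcome. Nothing in the article defines the phrase as missing follow-up.

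Correcting that phrase does not cure the second problem. A poor echo window is discovered only by doing the echo. In a comparison of TTE with no TTE, the criterion has no counterpart in the comparison group, where patients with the same trait are kept. An uninterpretable scan is also not a departure from the allocated strategy: the patient was allocated to TTE and received it. It is a result of the test under study, known only after allocation. If the trait is prognostic, removing it from one side spoils comparability.

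At stake is a supporting analysis that covers every endpoint. Readers take such an analysis as corroboration, and this one could lean towards TTE by construction.

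**Working it through.** **Inputs from the Sample size calculation section.** Control risk 4% in the RCT; a 50% relative reduction, hence 2% with TTE; 80% power; type I error 5% (two-sided, per Statistical analysis); 2% loss to follow-up; 2,330 patients. Equal allocation is assumed, because the text gives no ratio.

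**Reproducing the plan's figure.** Two proportions, pooled variance under the null, no continuity correction:

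n = [1.960·√(2·0.03·0.97) + 0.842·√(0.04·0.96 + 0.02·0.98)]² / 0.02² = 1,141 per arm.

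Inflated for loss: 1,141 / 0.98 = 1,165 per arm, or 2,330 in total. This matches the plan exactly. The evaluable set is 2 × 1,141 = 2,282.

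**Literal reading, primary endpoint only.**
- Expected TTE events: 1,141 × 0.02 = 22.8
- Expected control events: 1,141 × 0.04 = 45.6
- Patients left: 22.8 + 45.6 ≈ 68, or 68/2,282 = 3.0%

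All of them have the outcome. The risk is 100% in both arms and logistic regression has nothing to estimate. If secondary endpoints also count, the set is larger but still selected on outcome.

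**Charitable reading (missing assessment), with the poor-window exclusion kept.** The article gives neither the frequency of poor windows nor their relation to risk, so both are assumed. Let w be the share of the TTE arm excluded and m the risk of those patients relative to the remaining TTE patients. Suppose there is no true effect and 4% risk in both arms. The remaining TTE rate r satisfies r(1 − w) + m·r·w = 0.04, so

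r = 0.04 / (1 − w + w·m), and apparent RR = r / 0.04 = 1 / (1 − w + w·m).

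| w | m | 1 − w + w·m | TTE rate | Apparent RR |
|---|---|---|---|---|
| any | 1 | 1.000 | 4.00% | 1.00 |
| 3% | 1.5 | 1.015 | 3.94% | 0.985 |
| 5% | 2 | 1.050 | 3.81% | 0.952 |
| 10% | 2 | 1.100 | 3.64% | 0.909 |
| 10% | 3 | 1.200 | 3.33% | 0.833 |

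**Power.** With risk unchanged, dropping 5% or 10% of the TTE arm lowers power from 80.0% to 78.8% or 77.5%. The harm is bias rather than lost power.

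**The case against.** Nobody would run the literal rule. The paragraph says endpoints are to be tested in this set, which is impossible if every member has an event. A reader might infer that the plan intends to analyse only patients with events, but the documents do not support that. The phrase is loose English, very probably for missing endpoint assessment, and a full protocol or SAP that is not shown may say so. What remains is a stated rule that is wrong as printed.

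A reader might also infer that the whole rule cuts only the TTE arm. It does not. The poor window is introduced as an example, control patients given TTE could be excluded under the same clause, and missing outcomes can occur in both arms. One-sidedness belongs to the poor-window criterion alone.

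The bias may also be too small to see. With no effect and 45.6 events per arm, the standard error of log RR is √[2(1/45.64 − 1/1,141)] = 0.205, giving a 95% interval of about 0.67 to 1.49 around 1. A shift to 0.95 is lost in that, and the planned RR is 0.50. This stands as a limit on severity. It does not make the criterion sound, because the shift is systematic and its size is unknown.

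Finally, how the strategy performs when an interpretable TTE was obtained is a fair question, since the hypothesis works through discovery of abnormalities. But the no-TTE group offers no matching subset, so the question is better answered descriptively than by a between-group comparison.

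**Conclusion.** The rule is wrong as written, in a supplementary analysis. The wording on endpoints makes the set unusable if taken literally, and is almost certainly a slip. The poor-window criterion is the part that survives a charitable reading: it can remove patients only from the TTE group, on a post-allocation test result, although the strategy was delivered.

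If a poor window marks higher risk, the bias favours TTE, with a spurious RR of 0.985 to 0.83 across the assumed range and 0.95 at 5% excluded with twice the risk. These figures rest wholly on assumptions, and the bias is zero if the trait is unrelated to risk.

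It would be a mistake to conclude that the main result is compromised. The full analysis set follows the assigned group and keeps patients with poor windows. The sentence should be corrected before analysis, but the defect does not threaten the primary inference.

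**What to change.** Reword the per-protocol definition as follows:

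- Replace the exclusion of subjects without endpoints by exclusion of patients with unknown 30-day primary endpoint status.
- Delete the poor-window example and state that an uninterpretable TTE counts as TTE done.
- Define violations as not following the allocated strategy, in either arm: TTE not done in the TTE arm, or preoperative TTE done in the control arm. This applies to the RCT. In the cohort, TTE is discretionary, so there is no allocation to depart from.
- Do not add having had the index surgery as a criterion. The tertiary endpoint paragraph under Outcome definitions and follow-up lists delay or cancelation of surgery among the actions that TTE findings can prompt. Such a criterion would itself exclude patients differentially. For the same reason, an unoperated patient should not be classed as having unknown status on that ground alone.

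The cost is a few sentences: no new data, no extra patients and no change to the sample size. The downside is that the per-protocol set no longer isolates patients with an interpretable TTE. Their number and outcomes can be reported descriptively within the TTE group.

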### Outcome definitions and follow-up

The primary endpoint of this study is a composite of the incidences of all-cause death, aborted sudden cardiac arrest, type I MI, unstable angina, stress-induced cardiomyopathy, lethal arrhythmias (such as sustained ventricular tachycardia or ventricular fibrillation), and newly diagnosed or acutely decompensated heart failure (HF). Type I MI is defined as an increase of cardiac troponin I or T above the 99th percentile of the upper reference limit and at least one evidence of coronary ischemia including symptoms, new ST-T change or pathologic Q wave on an electrocardiogram, new regional wall motion abnormality (RWMA), or coronary thrombus on angiography or autopsy according to the fourth universal definition of MI [19]. Because there is no unified definition of stress-induced cardiomyopathy, we modified the Mayo Clinic Diagnostic Criteria to include more strict standards [20, 21]: (1) new ST-segment or T wave change, (2) an increase in cardiac troponin greater than three times the upper reference limit, (3) new RWMA in TTE, and (4) no evidence of significant coronary artery disease explanatory of new RWMA by coronary angiography/coronary computed tomography or evidence of recovery of RWMA in the following TTE. Decompensated HF is diagnosed based on symptoms or signs presenting with pulmonary edema, cardiogenic shock, or abnormal systolic/diastolic dysfunction after surgery [22].

Secondary endpoints include documented incidences of symptomatic arrhythmias, cerebrovascular accidents, transient ischemic attack, systemic embolism, pulmonary embolism, type II MI, or elevated N-terminal pro B-type natriuretic peptide (NT-proBNP) above 300 pg/ml. Documented symptomatic arrhythmias are defined as nonsustained ventricular tachycardia, newly detected atrial fibrillation (AF), or rapid ventricular response requiring additional medical therapy in patients with well-controlled AF. Myocardial injury equivalent to type II MI is defined as elevated troponin levels greater than the 3-fold upper limit of the normal value [19].

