In the present study, we provide new classifications of risk groups. Risk is redefined by merging the surgical risk and the clinical risk of individual participants. We also classified surgical risk more thoroughly by incorporating the organ system undergoing surgery and the known risk of individual surgery. With more detailed risk classifications, we expect more accurate postoperative risk assessment for individual surgeries. Moreover, less severe, but clinically significant, endpoints such as heart failure, stress-induced cardiomyopathy, cerebrovascular accidents, pulmonary embolism, and atrial fibrillation, are also included in this study; thus, we may be able to discover new common postoperative CVEs in the current medical landscape. To the best of our knowledge, there have been no large-scale RCTs or prospective cohort studies investigating the benefits of preoperative echocardiography. The results of this study may provide information on specific groups of patients who would benefit from preoperative echocardiography before noncardiac surgery. Additionally, all patients enrolled in the RCT and prospective cohort studies will undergo preoperative plasma NT-proBNP and troponin I or T evaluation. These biomarkers will be used for the assessment of primary and secondary outcomes as well as the possible predictor of the postoperative CVE risk.

In summary, the PREOP-ECHO trial will gather data regarding the use of preoperative echocardiography in patients undergoing intermediate- to high-risk noncardiac surgery. The results will help in developing models to predict the risk of postoperative CVE and expand postoperative CVEs to include heart failure, nonfatal arrhythmia, and stress-induced cardiomyopathy.

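### Two secondary components rest on a laboratory value alone, are sampled by protocol only within 3 days but recorded for 30, so unequal discretionary testing would bias them

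*Protocol article*

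**What the plan says.** Four parts of the protocol article bear on this point.

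- **Endpoint definitions** (Outcome definitions and follow-up). The secondary endpoints include "elevated N-terminal pro B-type natriuretic peptide (NT-proBNP) above 300 pg/ml". The same section adds: "Myocardial injury equivalent to type II MI is defined as elevated troponin levels greater than the 3-fold upper limit of the normal value". Neither definition asks for a symptom, an ECG or imaging finding, a change from the preoperative value, or a sample taken at a set time.
- **Scheduled sampling** (Data procurement). Troponin and NT-proBNP "will be gathered preoperatively within 90 days before surgery and postoperatively within 3 days after surgery". From then to day 30, Outcome definitions and follow-up provides for telephone or clinic contact and mentions no blood sample.
- **Recording window** (Statistical analysis, under the heading for the high-risk cohort). "All individual components composing primary and secondary endpoints occurring within 30 days after index surgery are documented with the date of occurrence". The next sentence has each component analysed separately by logistic regression, which is an ever/never outcome. The surrounding text covers analysis by assigned group, so it applies to the RCT as well.
- **Discretionary testing** (Randomization and stratification). In both studies, "usual postoperative care including drug prescriptions or laboratory examinations can be performed as circumstances demand". Physicians act on the echocardiography result when choosing the next diagnostic step (Outcome definitions and follow-up). In the cohort they also decide whether echocardiography is done at all.

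**The concern.** A patient can record a threshold-only event after day 3 only if someone orders a test. Each extra test is one more chance to cross the threshold, and a patient who is not tested again cannot record a late event. The recorded rate therefore depends partly on how often blood is drawn.

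That does no harm to the comparison if testing is equally frequent in both groups. The design gives no assurance of this. Randomization balances patients at baseline, not tests ordered afterwards by clinicians who can know whether echocardiography was done and what it showed. In the cohort, the physicians who choose echocardiography may also choose more follow-up tests.

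The planned safeguards do not reach the problem. Propensity score matching is planned for the primary endpoint only. Adjudication cannot undo an extra test when the definition is a bare threshold. At stake is the interpretation of two secondary components: a difference, or the absence of one, could reflect testing practice rather than postoperative cardiac state.

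**Working it through.** **1. Number per arm.** The article gives no expected rate or testing frequency for the laboratory components, so the only figure to reproduce is the RCT sample size. Inputs from Sample size calculation: 4% against 2% (a 50% reduction), 80% power, 5% type I error, 2% loss. The two-sided test is from Statistical analysis.

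n = [1.960 × √(2 × 0.03 × 0.97) + 0.842 × √(0.04 × 0.96 + 0.02 × 0.98)]² / 0.02² = 1,141 per arm

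1,141 / 0.98 = 1,165 after rounding up, and 2 × 1,165 = 2,330, as stated. The illustration below uses 1,141 per arm.

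**2. Model with no true difference.** Let

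- s = share positive on the scheduled sample within 3 days;
- t = share tested again on days 4 to 30;
- q = chance that a late test is positive in someone not yet positive.

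Recorded rate = s + (1 − s) × t × q

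Biology (s and q) is the same in both groups; only t differs. **All three are assumptions**, because the article gives none of them. The groups are labelled A and B, since the article does not say which would be tested more.

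The chance of a false significant result comes from a two-sample z test with d = |a − b| / √{[a(1 − a) + b(1 − b)] / 1,141}, as Φ(d − 1.96) + Φ(−d − 1.96).

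**3. Worked example.** With s = 5%, q = 10%, and t = 40% in A against 20% in B:

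- a = 0.05 + 0.95 × 0.40 × 0.10 = 0.088
- b = 0.05 + 0.95 × 0.20 × 0.10 = 0.069
- d = 0.019 / 0.01125 = 1.69, so the chance of a false significant result is about 39%
- extra recorded events in A = 0.019 × 1,141, about 22

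**4. Range of scenarios.**

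| s | q | t, A vs B | Recorded, A vs B | Difference (points) | Odds ratio | Chance of p < 0.05 |
|---|---|---|---|---|---|---|
| any | any | 20% vs 20% | equal | 0 | 1.00 | 5% |
| 40% | 5% | 30% vs 20% | 40.9% vs 40.6% | 0.3 | 1.01 | 5% |
| 40% | 5% | 40% vs 20% | 41.2% vs 40.6% | 0.6 | 1.03 | 6% |
| 5% | 10% | 30% vs 20% | 7.9% vs 6.9% | 0.95 | 1.15 | 14% |
| 5% | 10% | 40% vs 20% | 8.8% vs 6.9% | 1.9 | 1.30 | 39% |
| 20% | 20% | 40% vs 20% | 26.4% vs 23.2% | 3.2 | 1.19 | 43% |
| 10% | 20% | 40% vs 20% | 17.2% vs 13.6% | 3.6 | 1.32 | 67% |
| 5% | 40% | 40% vs 20% | 20.2% vs 12.6% | 7.6 | 1.76 | above 99% |

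The second and last rows are the extremes of the grid examined (s from 5% to 40%, q from 5% to 40%, unequal re-testing of 30% or 40% against 20%). The effect is negligible when most positives are already found by day 3 and late tests are seldom positive. It is large when the reverse holds.

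**5. Effect of fixing the sample.** If only the scheduled sample counts, the term (1 − s) × t × q drops out. The recorded rate is then s in both groups and the odds ratio is 1.00, however unequal later testing is. The sample size is unchanged, because it rests on the primary endpoint.

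**The case against.** The strongest reply is that the 30-day sentence is a rule about recording dates, not a rule that any discretionary laboratory value is an endpoint. On that reading the 3-day results are the source for the laboratory components, later contacts capture clinical events, and the detail sits in the full protocol or the case report forms. The reading is sensible, but the article does not state it. The sentence covers all components of the secondary endpoints without exception, and the next one analyses each component. The article itself sets the thresholds, the sampling window and the recording window, and taken together they admit late unscheduled values.

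A reader might go further and infer that the echocardiography arm will be tested more, that a patient without echocardiography usually has one test, and hence that the bias runs against echocardiography. The documents do not support this. The usual-care provision applies to both studies and names no group. An abnormal scan could prompt more tests, but a normal one could reassure and reduce them, so the bias could hide a benefit or exaggerate one.

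Three further limits stand:

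- The size rests on assumed inputs. The Discussion expects few significant abnormalities where none is suspected. If unequal testing in the RCT arose only through abnormal scans, the re-testing gaps used above would probably be too wide.
- Patients with abnormal scans may already be positive on the early sample, and then extra tests add nothing.
- The scope is narrow. Type I MI and stress-induced cardiomyopathy in the primary composite need evidence beyond troponin, and all-cause death is unaffected. Because components are analysed separately, an effect confined to the laboratory components would be visible.

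**Conclusion.** The concern holds for two secondary components. As written, NT-proBNP above 300 pg/ml and troponin above three times the upper limit can be met by any value up to day 30, while protocol sampling is confined to the first 3 days and the rest is discretionary. If testing frequency differs between groups, the group tested more records more of these events without any true difference.

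Neither direction nor size can be derived from the article. Under the assumed inputs the spurious difference runs from 0.3 to 7.6 points, and it is zero if testing is equal. The primary composite is little affected, and the sample size of 2,330 is untouched. This does not threaten the main conclusion, but it should be corrected because the remedy is cheap.

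**What to change.** - Define the two laboratory-only components, in both groups and both studies, from the protocol-scheduled postoperative sample within 3 days.
- Prespecify which value counts if several exist in that window, for example the first scheduled draw and not the peak of all draws. Data procurement does not say that only one sample is taken, and taking the peak would bring the same problem into the first 3 days.
- Let unscheduled or later values count only as support for an adjudicated clinical event such as MI or heart failure.
- Report the number of postoperative troponin and NT-proBNP tests by group, so that any difference in testing can be seen.

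The change takes a few sentences in the endpoint definition and one descriptive table. It needs no extra blood tests or patients. The price is that late or unscheduled silent elevations are no longer counted; under the present text they are captured only when someone happens to test.
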